# P3MC: A double blind parallel group randomised placebo controlled trial of Propranolol and Pizotifen in preventing migraine in children

**DOI:** 10.1186/1745-6215-11-71

**Published:** 2010-06-16

## Abstract

**Background:**

A recent Cochrane Review demonstrated the remarkable lack of reliable clinical trials of migraine treatments for children, especially for the two most prescribed preventative treatments in the UK, *Propranolol *and *Pizotifen*.

Migraine trials in both children and adults have high placebo responder rates, e.g. of 23%, but for a trial's results to be generalisable "placebo responders" should not be excluded and for a drug to be worthwhile it should be clearly superior, both clinically and statistically, to placebo.

**Methods/Design:**

Two multicentre, two arm double blind parallel group randomised controlled trials, with allocation ratio of 2:1 for each comparison, Propranolol versus placebo and Pizotifen versus placebo. The trial is designed to test whether Propranolol is superior to placebo and whether Pizotifen is superior to placebo for the prevention of migraine attacks in children aged 5 - 16 years referred to secondary care out-patient settings with frequent migraine (2-6/4 weeks). The primary outcome measure is the number of migraine attacks during trial weeks 11 to 14.

**Discussion:**

A strength of this trial is the participation of clinically well defined migraine patients who will also be approached to help with future longer-term follow-up studies.

**Trial Registration:**

ISRCTN97360154

## Background

In the last 20 years the International Headache Society (IHS) has fostered the development of high quality research in headache including migraine. The 2004 (2^nd^) edition of the International Classification of Headache Disorders [1] provides a framework for headache research, including clinical trials. It is vital that trials use this classification which has become rather more child relevant in this last edition.

Inclusion of patients with Probable Migraine (PM), as defined in the classification, previously called "migraine-like headache" or "mixed headache" is vital for the trial to be of general use to most children presenting to paediatricians with severe headaches, because many general paediatricians will be unfamiliar with the precise operational criteria for Migraine subtypes.

A recent Cochrane Review [2] has demonstrated the remarkable lack of reliable clinical trials of migraine treatments for children, especially for the two most prescribed preventative treatments used in the UK, Propranolol and Pizotifen.

For a trial's results to be generalisable it should reflect the high placebo responder rates (around 23% [3]) typically found and not exclude "placebo responders". In addition for a drug to be worthwhile it should be clearly superior, both clinically and statistically, to placebo.

The clinical course of migraine is especially difficult to predict in children. Migraine will come for weeks, months or a few years then remit for months or years, sometimes returning unpredictably later on. Long term follow-up is difficult and studies have demonstrated this variability [4].

The aim of this trial is to confirm or refute superiority of Propranolol to placebo and of Pizotifen to placebo for the prevention of migraine attacks in children aged 5 - 16 years referred to secondary care out-patient settings with frequent migraine (2-6/4 weeks).

Both the active trial treatments or "Investigational Medicinal Products" (IMPs), Propranolol and Pizotifen have been in common clinical use for this indication in children for over 20 years. The trial does not therefore expose this group of patients to a new therapeutic risk, but will systematically evaluate efficacy and adverse events. The results will ascertain if one or both are superior to placebo in the prevention of migraine in children, and quantify other useful clinical outcomes such as quality of life, school attendance, any prolonged benefit after drug withdrawal, and adverse effects.

## Methods/Design

### Study design

Two simultaneous multicentre parallel group double-blind randomised placebo controlled trials of Propranolol and Pizotifen.

### Setting

Secondary care paediatric headache or neurology clinics.

### Participants

#### Inclusion criteria

1. age 5 years 0 months to 16 years 11 months

2. with Migraine with Out aura (MO), Migraine with Aura (MA), Probable Migraine (PM) as defined by IHS [1] (see Appendix E),

3. with 2 to 6 migraine or probable migraine attacks/4 weeks by history during the previous 3 months

4. and 2 to 6 migraine or probable migraine attacks/4 weeks during the 4 week run-in

5. and treating paediatrician and parent/guardian and child or young person believe the attacks are currently frequent and severe enough to merit a try of twice daily preventative medication

6. Satisfactory completion of headache diary during the run-in period at discretion of the investigator

#### Exclusion criteria

1. Asthma, bronchospasm or nocturnal or exercise induced cough or wheeze within the last 12 months or currently on daily asthma preventative treatment

2. children under paediatric cardiology review, at the discretion of their paediatric cardiologist, e.g. if Propranolol or Pizotifen were contraindicated

3. children with any of the following: uncontrolled heart disease, the presence of second or third degree heart block, in cardiogenic shock, bradycardia, severe peripheral arterial disease, metabolic acidosis, sick sinus syndrome, untreated phaeochromocytoma, prone to hypoglycaemia (e.g. after prolonged fasting) or Prinzmetal's angina.

4. previous severe adverse event probably related to Propranolol or Pizotifen

5. on Propranolol, another beta-blocker, Pizotifen or Cyproheptidine in the last 3 months

6. currently in or have been in another prospective drug trial in the last 3 months

7. fewer than 2 or more than 6 eligible attacks during the 4 week run-in, and stay excluded for 3 months at least

8. child or family unable to identify their migraine or probable migraine headaches confidently (as may happen with some patients with both mild headaches and migraine on different days, e.g. with chronic daily headache [15 or more headache days/month]).

9. females of child bearing potential who are not using a reliable contraceptive strategy such as abstinence, barrier methods, oral contraceptive pills and contraceptive injections. See Pregnancy section below.

10. Informed consent not given by parents/guardian, or assent/consent not given by patient

### Interventions

#### Propranolol

A non-selective beta-blocker which crosses the blood-brain barrier exerting central as well as peripheral effects and which has been used in migraine prevention since the 1960s [5]. It is generally well tolerated but in high dose can be associated with fatigue or sleep disturbance. It can also cause bronchospasm and exacerbate asthma.

#### Pizotifen

An antihistamine with histamine-1 antagonist and serotonin (5-HT2) antagonist properties that is structurally related to the tricyclic antidepressants. It has been used for over 20 years in the United Kingdom for migraine prophylaxis in children, young people and adults. It is generally well tolerated but can cause drowsiness, so it is commonly given as a once a day evening dose. Other adverse effects include increased appetite and weight gain.

#### Placebo

Both liquid and tablet formulations of the placebo will be manufactured using the same excipients used in the active formulation of the drugs minus the active ingredients. The placebo, Propranolol and Pizotifen tablets are matched in appearance; the liquid placebo matches the liquid Propranolol in appearance and taste but the liquid Pizotifen has a slightly different flavour.

All participants will be offered a choice of liquid or tablet preparations of the trial treatments. Because Pizotifen only has an evening dose, while Propranolol is given twice daily, to maintain blinding participants in the Propranolol and placebo arms will receive morning and evening doses from separate bottles; those in Pizotifen arm will take a morning placebo dose and an active evening dose (also from separate bottles).

For both active arms in this trial, starting, titration and age specific maintenance doses are consistent with the recommendations in "Medicines for Children" [6] and the new "British National Formulary (BNF) for children" [7] for 80% of participants by standard growth charts for the tablet preparations. The maximum dose of the liquid preparation is less to comply with World Health Organisation (WHO) recommendations on maximum intake of propylene glycol (used as a preservative for the liquid preparation of Propranolol).

### Concomitant therapy

#### Permitted medication

Any other regular medication (apart from Propranolol or other beta blocker, Pizotifen or Cyproheptidine in the 3 months before recruitment)

Other migraine preventative medication should normally be withdrawn first, but it may be continued as long as the dose does not change during the 12 week assessment.

#### Rescue medication and additional treatment(s)

All participants will be given an individual rescue treatment plan for migraine headaches, depending on their and their paediatrician's experience and preference. All rescue treatments used and their doses and effects will be recorded in the diary during the 4 weeks baseline assessment block 1 and the assessment blocks 2, 3 and 4 (weeks 11-14, 25-28, 37-40).

### Restrictions

Rizatriptan should be avoided by the trial participants while taking the trial treatments and for 5 days after stopping the trial treatments, because of a drug interaction with Propranolol.

Different non-steroidal anti-inflammatory drugs (NSAIDs) should not be used together. Aspirin should be avoided in children under 16 years. Use of any over-the-counter remedies will be checked by the research nurse.

#### Compliance

This will be assessed in 2 ways:

1) by verbally questioning the participant and parent/guardian at visits as to roughly how often a week a dose is missed. The % compliance is defined as 100 - % missed doses.

2) by examination of returned medication bottles, and measurement of the observed residual tablet numbers or residual liquid volumes. Missed doses by tablet number or volume will be expressed as:.

S = amount supplied,

R = amount returned

P = amount planned to be taken

The level of acceptable compliance with study medication will be set at >50% on both measures for the main outcome assessment period (weeks 11-14).

#### Criteria for terminating trial

The study may be stopped as a whole because of a regulatory authority decision, change in opinion of the REC or overwhelming evidence of efficacy/inefficacy, safety concerns or issues with trial conduct at the discretion of the Sponsor.

Recruitment at a centre may be stopped particularly for reasons of low recruitment, protocol violation or inadequate data recording.

### Hypotheses

#### Primary hypothesis

• To test whether Propranolol or Pizotifen are superior to placebo for the prevention of migraine attacks in children aged 5 - 16 years old with frequent migraine (2-6/4 weeks), who are referred to secondary care out-patient settings.

#### Secondary hypotheses

• To test whether any therapeutic effect out lasts the period of drug administration.

• To test whether a dose (in mg/kg/day) - response relationship exists at the doses used.

• To test whether active treatment improves participation by school attendance, and parent/guardian time off work, and health related and non-health related quality of life, and health status.

• To estimate cost-effectiveness if either active treatment proves superior to placebo.

### Sample size

The number of attacks per month is assumed to follow an over-dispersed Poisson distribution. A mean attack rate in the last month of treatment of 3 episodes with variance of 4 was assumed for the placebo arms based on the review of Victor & Ryan (2003) [2].

The sample size for the primary endpoint was estimated using formula 9.13 on page 176 of Machin et al [8] assuming a 33% reduction in the attack rate in the active arms. This formula gives the total number of attacks that must be observed based on a Poisson distribution, and this was divided by 2.5 (average number of attacks per person) to give the total number of participants in each study.

The over-dispersion in comparison with a Poisson distribution was allowed for by multiplying the required number of participants based on the standard formula by a factor of 1.33.

The sample size estimates for each trial assumed a power of 80% and 5% two-sided significance, with a 2:1 allocation of active: placebo treatment within each trial.

On these assumptions the required sample size is 226 evaluable participants for each trial, i.e. 452 in total, to detect a reduction in mean attack rate in both arms from 3 to 2 per month.

The target of 600 for recruitment also leaves a margin for drop out of up to 25% (=1-452/600) for the primary outcome but only 2% (=1-588/600) for the proportion of responders outcome.

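### The stated 226 participants per trial do not follow from the stated inputs (3 to 2 attacks, 80% power), which give about 102 to 134; effect, power or size is misstated

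*Protocol article*

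**What the plan says.** All the inputs stand in the sample size section of the protocol article.

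- Placebo arm: "A mean attack rate in the last month of treatment of 3 episodes with variance of 4 was assumed for the placebo arms".
- Effect: the event formula was applied "assuming a 33% reduction in the attack rate in the active arms", and the section later restates this as 3 falling to 2 per month.
- Error rates and allocation: the estimates "assumed a power of 80% and 5% two-sided significance, with a 2:1 allocation of active: placebo treatment within each trial".
- Conversion to participants: of the total number of attacks, the section says "this was divided by 2.5 (average number of attacks per person", bracket closing there. The result is then multiplied by 1.33 for over-dispersion.
- Result: "On these assumptions the required sample size is 226 evaluable participants for each trial, i.e. 452 in total".
- Recruitment: the target of 600 is said to leave a "margin for drop out of up to 25% (=1-452/600) for the primary outcome", and a margin of 2% for the responder outcome, which needs 588.

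The event formula is cited from a textbook by equation and page number but is not printed.

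**The concern.** The section gives every input and then presents 226 as their consequence, so the figure can be tested. It fails by a factor of roughly 1.5 to 2.2, far more than the spread between standard formulas.

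This is the justification for the primary endpoint in a trial that randomises children. As written, a reader cannot tell whether the design has 80% power for a one-third reduction or for about a one-quarter reduction. The total of 452 and the 25% drop-out margin both inherit 226. The analysis section also points back to the sample size justification when it sets the significance level.

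**Working it through.** **Inputs** (protocol article, sample size section): placebo mean 3, variance 4; active mean 2, so rate ratio RR = 2/3 (0.67 if 33% is taken literally); two-sided 5% (z = 1.960); power 80% (z = 0.842); 2:1 allocation; divisor 2.5; multiplier 4/3 = 1.33. Then (1.960 + 0.842)² = 7.849.

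**Step 1. Work back from the plan's figure.** The recipe is N = events / 2.5 × 1.33. For N = 226, events = 226 / 1.33 × 2.5 = 425.

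**Step 2. Events needed for RR = 2/3.** Because the cited formula is not printed, I use the usual alternatives.

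- Log-ratio (Schoenfeld) form: E = 7.849 / [(2/3)(1/3)(ln RR)²] = 7.849 / (0.2222 × 0.1644) = 215.
- Freedman-type form: E = 7.849 × (1 + φRR)² / [φ(1 − RR)²], with φ the allocation ratio. The factor after 7.849 is 24.5 for φ = 2, 25 for φ = 1 and 32 for φ = 0.5.

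| Form | Events | N = events / 2.5 × 1.33 |
|---|---|---|
| Freedman-type, φ = 2 | 192 | 102 |
| Freedman-type, φ = 1 | 196 | 104 |
| Log-ratio | 215 | 114 |
| Freedman-type, φ = 0.5 | 251 | 134 |

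Formulas that compare two Poisson rates directly, multiplied by 1.33, give 111 to 125. The highest figure comes from combining RR = 0.67, φ = 0.5 and the 2:1-weighted divisor (3 + 2 × 2.01)/3 = 2.34, which gives about 146. Nothing at 80% power and a 33% reduction comes near 226.

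**Step 3. Power for 3 versus 2 at 226 evaluable.** Split 2:1 (150.67 and 75.33), taking variance/mean = 4/3 in both arms:

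SE(log RR) = √{1.333 × [1/(150.67 × 2) + 1/(75.33 × 3)]} = 0.1016.

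0.4055 / 0.1016 − 1.96 = 2.03, a power of 97.9%. Using 425 events instead, the log-ratio form gives 97.6% and the Freedman-type forms 95.4% (φ = 0.5) to 98.6% (φ = 2). The unpooled Poisson form gives 96.4%. A gamma-Poisson simulation with a robust test (20,000 runs) gave 97.4%. The range is therefore about 95-99%.

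**Step 4. Effect detectable with 80% power at 226.** In log-ratio form, RR = exp[−2.802 / √(425 × 0.2222)] = 0.75. Across the forms it runs from 0.737 to 0.761, a reduction of about 24-26%.

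**Step 5. The divisor.** Average attacks per person with means 3 and 2:

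- equal weights: (3 + 2)/2 = 2.5;
- 2:1 weights, as the design has: (3 + 2 × 2)/3 = 2.33.

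**Step 6. What could have produced 226.** Three readings fit, each under some formula:

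| Reading | Result |
|---|---|
| 25% reduction (3 to 2.25), 80% power | 427 events, N = 227 (log-ratio); 230 (unpooled Poisson); 205 to 253 under other forms |
| 33% reduction (RR 0.67), 95% power | 425 events, N = 226.3 (Freedman-type, φ = 0.5); 174 to 212 under other forms |
| 33% reduction, 80% power, both trials together | 2 × 114 = 228 (log-ratio) |

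**Step 7. Figures that depend on 226.** The arithmetic of the margin is right: 1 − 452/600 = 24.7%. If 226 were the total for both trials, it would become 1 − 226/600 = 62.3%.

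**The case against.** The strongest reply is that the cited formula cannot be seen, that the error is on the safe side, and that nothing in the conduct of the trial depends on it. Most of this stands. The primary comparison is not underpowered for the stated effect. A null result will be judged by the confidence interval from the Poisson model, not by the planning effect. The recruitment target was also set against 588 for the responder outcome, so 600 does not rest on 226 alone. But the hidden formula does not rescue the figure: every standard form falls well short of 226, and they differ from one another far less than any of them differs from it.

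A reader might infer more: that the trial was really sized for a 25% reduction, because 3 to 2.25 gives about 227 and a 2:1 average of exactly 2.5, and because 3/2.25 = 1.33 could have been written up as a 33% reduction. The article does not support this. The rate 2.25 appears nowhere in it, and the effect is stated twice and consistently as 33% and as 3 to 2. The divisor 2.5 is also the plain mean of 3 and 2. Two other readings reproduce 226 about as well, and the 25% reading itself works only under some of the formulas. It is a good candidate, not a demonstrated cause.

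Nor should a reader infer a shortfall from the divisor. Replacing 2.5 by 2.33 at the stated effect and power still leaves N at no more than about 143 for RR = 2/3 (251 / 2.33 × 1.33).

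**Conclusion.** The statement is wrong as written. On its own assumptions the section supports about 102 to 134 participants per trial (about 146 at the extreme), not 226. With 226 evaluable, power is about 95-99% for 3 versus 2, and 80% power applies to a reduction of about 24-26%. Separately, 2.5 is not the average attack count under 2:1 allocation with means of 2 and 3.

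The document cannot show whether the effect, the power or the size is the wrong entry. The error is conservative for the stated effect, and correcting it calls for no change to recruitment.

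The conclusion rests on the cited formula being one of the standard event or Poisson-rate forms, and on the over-dispersion ratio of 4/3 applying to both arms.

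**What to change.** Keep the recruitment target. Recover the sponsor's calculation, then restate effect, power, formula, average attacks per person and N so that they agree. If 226 evaluable per trial is confirmed, one of two wordings would be consistent:

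- about 97% power (95-99% depending on the formula) to detect 3 to 2 attacks, with an average of 2.33 attacks per participant; or
- about 80% power to detect about a 25% reduction (3 to 2.25), with an average of 2.5.

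If the calculation shows that 226 was the total for both trials, the 452 and the 25% drop-out margin must be recomputed as well. The cost is a search for the calculation and the rewording of one paragraph. Randomisation, analysis and recruitment stay as they are.

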### Randomisation and blinding

The randomisation will be based on a computer generated pseudo-random code using random permuted blocks of randomly varying size, created by the Nottingham Clinical Trials Unit (CTU) in accordance with their standard operating procedure (SOP) and held on a secure server. The randomisation proceeds in two stages: firstly a randomisation to one trial or the other; secondly a randomisation within each trial to active or placebo arm. The randomisation within each trial will be stratified by age (5-11 years *vs *12-16 years), type of migraine (two categories) and recruiting centre (10 centres).

Investigators will access the treatment allocation for each participant by means of a remote, internet-based randomisation system developed and maintained by the Nottingham CTU. The sequence of treatment allocations will be concealed until interventions have all been assigned and recruitment, data collection, and all other trial-related assessments are complete.

### Procedures and observations

#### Consent

The process for obtaining participant informed consent or assent and parent/guardian informed consent will be in accordance with the REC guidance, and Good Clinical Practice (GCP) and any other regulatory requirements that might be introduced.

Potential participants will be identified in clinic based on their clinical diagnosis and history of migraine or probable migraine attack frequency for the previous 3 months. If the potential participant and their parent/guardian are willing to participate but cannot estimate the migraine attack frequency in the previous 3 months they will be given a standard headache diary to complete over the next 3 months, and appropriate advice and treatment will be given as is normal practice.

In the event of their withdrawal data collected so far will not be erased and will be used in the final analyses where appropriate (this will be explained in the Participant and Parent/Guardian Information Sheets).

### Baseline measurements

1. A standard headache diary will be completed by the participant and their parent/guardian. This is adapted for the trial from a migraine clinic diary developed by the British Paediatric Neurology Association's (BPNA's) Governance & Audit group [9].

2. Headache intensity scale [10] - a four point self-rated scale (assisted if needs be by the parent/guardian). This is the functionally based scale recommended by the IHS to assist in diagnosis, monitoring treatment clinically and in trials.

3. Pediatric Migraine Disability Assessment Scale (PedMIDAS), a standardised validated health-related quality of life scale for children with migraine [11].

4. Generic Child Quality of Life Measure (GCQ10), a standard validated non-health related quality of life scale for children [12].

5. EQ-5D [13], a standardised validated health outcome measure providing a simple descriptive profile and a single index value for health status. For parents/guardians and participants aged 12-16 years old.

6. Child-friendly EQ-5D [14] For younger participants; a child friendly version of EQ-5D has been developed and will be used during the trial for participants aged 7-11 years.

7. UK Proxy EQ-5D [15]

8. Age, sex, height, weight, blood pressure and heart rate at baseline and at all clinical visits

9. Parent's/guardian's stage at leaving full-time education

10. Full post code (to derive deprivation score for area of residence).

11. Office of National Statistics (ONS) self-coded NS-SEC of one parent/guardian [16]

